### Primary outcomes/behavioral

Assessment of health behaviors affecting hypertension, such as healthy diet, physical activity level, checking and monitoring BP, adherence to treatment, and predisposing factors, enabling factors and reinforcing factors contributing to adherence to treatment, and smoking cessation.

#### Adherence to antihypertensive medication use

This will be assessed with the Hill-Bone High Blood Pressure Therapy Compliance Scale, which includes 14 items, at the initial and final assessments [9–11]. Individuals will score from 14 to 56. An increase exceeding 20 % of the Compliance Scale score is considered effective.

#### Adherence to the DASH and low-sodium diets

A couple of questions in the baseline and final questionnaires will evaluate this. A 20 % rise in the score in this section is considered desirable.

#### Physical activity

The change and sequence of physical activity will be evaluated through a couple of questions in the questionnaire, at the baseline assessment and at the 8^th^ and 24^th^ weeks.

#### Regular BP monitoring

BP can be regularly monitored by regularly measuring and saving the relevant data in the mobile app. For every timely registration a score will be awarded. This part of the study is 60 days long. The participants will be asked to measure and register their BP once every other day. A score of 25 and higher will be considered appropriate.

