**Methods/design:**

A two-arm, parallel-design randomized controlled clinical trial will be conducted on 30 to 60 year-old patients with primary hypertension who are attending the Tehran Heart Center. One hundred and thirty-two (132) patients will be randomly assigned to the intervention and control (usual method) groups. The most important inclusion criteria are, having primary hypertension and being pharmacologically treated for it, and not having developed the complications of hypertension, such as myocardial infarction, cerebral stroke and cardiac insufficiency. The participants should be able to read Persian and be able to use the application.

The most important outcomes of the study include adherence to treatment, weight control, and regular monitoring of blood pressure which are assessed in the primary assessment (baseline data questionnaire) and again at the 8^th^ and 24^th^ weeks. The intervention is a mobile application that has capabilities such as reminders and scientific and supportive information.

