### Study setting

The participants will be selected from the patients attending the Tehran Heart Center Clinic. The Tehran Heart Center is a tertiary-care, educational subspecialty center for CVD affiliated with Tehran University of Medical Sciences. It has 460 beds and is one of the most well- equipped, specialized care centers for CVD in the region. Annually, an average 113,316 outpatients, 23,879 inpatients and 4331 open-heart surgery candidates are treated at the center [8].

The outcomes of the study (adherence to treatment, weight loss, regular BP monitoring) will be evaluated at the primary assessment (baseline data questionnaire) and again at the 8^th^ and 24^th^ weeks (Fig. 1).

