## Intervention

### Intervention and control groups

In addition to the usual care, the participants of the intervention group will receive the educational, supportive mobile application-based intervention (Additional file 2). The participants will have these applications for 6 months and the aforementioned measurements will be registered in it. Reminders for dose and time of drug intake, date of clinical visit, and other reminders will be activated. The users will be provided with the scientific information and skills required to identify the disease and its methods of control by the mobile application.

The participants in the comparison arm will receive the usual standard care based on the Joint National Committee (JNC) guideline. The usual care includes, measuring the patient’s BP, necessary assessments based on the patient’s history and circumstances, the specialist physician’s judgment, medication prescription, and other medical measures. The number of appointments and assessments in each group will be the same. The intervention and control participants’ appointment days will differ and the members of one group will not be in touch with those of the other.

The BPMAP application contains educational content that is meant to raise the level of knowledge in hypertensive patients regarding its complications and methods of control. Moreover, it contains supportive measures such as important reminders for time of drug use, smoking cessation, and weight loss.

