### Follow-up

The participants will be examined seven times at 2-week intervals (Table 1). In the first visit, after ensuring the participant’s inclination to participate in the study and after the informed consent form is completed, the baseline data questionnaire will be completed by the researcher. Clinical measurements, such as systolic and diastolic BP, waist circumference and hip circumference, BMI, and biochemical measurements, such as LDL, HDL, and total cholesterol levels, will be performed.

**Table 1 Tab1:** Steps taken in each visit

	Study period										
	Enrollment	Allocation	Post allocation								Close-out
Week	−1 to 0	0 ± 2 days	2 ± 2 days	4 ± 2 days	6 ± 2 days	8 ± 2 days					24 ± 2 days
Time point	1^st^ visit	2^nd^ visit	3^rd^ visit	4^th^ visit	5^th^ visit	6^th^ visit					7^th^ visit
Enrollment:	×										
Eligibility screen	×										
Informed consent	×										
Allocation	×										
Intervention		×	×	×	×	×	×	×	×	×	×
Assessment	×					×					×
Baseline variables	×					×					×
Measuring adherence to treatment	×					×					×
Measuring adherence to the diet	×					×					×
Evaluating the predisposing, enabling, and reinforcing factors of adherence	×					×					×
Measurement of systolic and diastolic BP, waist circumference, and BMI	×	×	×	×	×	×	×	×	×	×	×
Evaluating the regular monitoring of BP by the mobile application	×	×	×	×	×	×	×	×	×	×	×
Evaluating the usability of the software						×					×
Evaluating the level of satisfaction of the software/application						×					×

*BMI* Body Mass Index, *BP* blood pressure

The 2nd visit will be made a week after the first. The application will be installed on the cell phones of the intervention group’s patients and its operation will be taught to them. Any problems that arise will be dealt with accordingly. Moreover, the sphygmomanometer used by the patient at home will be evaluated for its precision and sensitivity (calibration). In order to ensure that the patients measure their BP correctly at home, the methods applied by them will be controlled, and if faulty, corrected. Clinical measurements and usual care will be performed. The usual care includes history taking, BP measurement, and diagnostic and therapeutic measures based on the JNC guideline on high blood pressure.

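### The only scoring rule for regular BP monitoring counts app registrations, which controls cannot make and which cannot exist at baseline, so it cannot support the planned baseline-adjusted comparison between arms

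*Protocol article*

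**What the plan says.** **Status of the outcome.** The abstract states: "The most important outcomes of the study include adherence to treatment, weight control, and regular monitoring of blood pressure". Study setting repeats the three and gives the timing: "The outcomes of the study (adherence to treatment, weight loss, regular BP monitoring) will be evaluated at the primary assessment (baseline data questionnaire", then again at weeks 8 and 24. Primary outcomes/behavioral includes it in its list: "healthy diet, physical activity level, checking and monitoring BP, adherence to treatment".

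**How it is scored.** Regular BP monitoring says: "BP can be regularly monitored by regularly measuring and saving the relevant data in the mobile app". It continues: "For every timely registration a score will be awarded" and "This part of the study is 60 days long". Participants are asked for one entry every second day, and a score of at least 25 counts as adequate. The matching row of Table 1 (Follow-up) reads "Evaluating the regular monitoring of BP by the mobile application" and is marked at every visit, including visit 1.

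**Who has the app.** Under Follow-up, the app is installed at visit 2, on the phones of intervention patients only. For controls, Intervention and control groups says: "The participants in the comparison arm will receive the usual standard care".

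**How arms are compared.** Statistical methods specifies analysis of covariance adjusted for the baseline score for all quantitative variables, chi-squared tests between the groups for the qualitative ones, and multiple imputation for lost data. It makes no exception for this outcome.

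**The concern.** An outcome compared between arms has to be obtainable in the same way in both. Here the one stated rule counts entries in a tool that is itself the intervention. A control who measures BP at home every second day would score zero or have no score, exactly like a control who never measures. The contrast would then reflect possession of the app and not monitoring behaviour.

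The neighbouring behavioural outcomes (diet, physical activity, smoking, predisposing and related factors) are each expressly assigned to questionnaire items, which both arms can answer. BP monitoring is not. At stake is whether one of the three headline outcomes can answer its question at all.

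**Working it through.** The plan states no power or effect size for this outcome, so there is no figure of its own to reproduce. The check sets the sections side by side and then shows the consequence of each way of treating controls.

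**1. Consistency of the sections**

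| Question | Regular BP monitoring and Table 1 | Elsewhere in the article |
|---|---|---|
| Instrument | App registrations | Study setting places the outcome at the baseline questionnaire. Outcome measures lists a questionnaire and physical or laboratory measurements, and not the app |
| Control value | None possible | Statistical methods compares the two groups |
| Baseline value | Table 1 marks visit 1, but the app arrives at visit 2 | Study setting requires one, and the covariance analysis adjusts for it |
| Time points | One 60-day window | Baseline, week 8, week 24 |

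The window is 60/7 = 8.6 weeks. It roughly fits the week 8 assessment and gives no defined score for week 24.

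**2. The score**

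One entry every second day for 60 days gives 60/2 = 30 entries. With one point per entry (assumed, since the points per entry are not stated), the maximum is 30 and the threshold is 25/30 = 83%.

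**3. If controls are scored zero**

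Inputs: 66 per arm (Randomization), two-sided 5% level (Sample size), and k intervention patients reaching 25 against 0 controls.

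For k/66 against 0/66 the uncorrected chi-squared statistic reduces to 132k/(132 − k):
- k = 3: 396/129 = 3.07, p = 0.080
- k = 4: 528/128 = 4.125, p = 0.042

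The two-sided Fisher p-value is 2 × C(66,k)/C(132,k):
- k = 5: p = 0.058
- k = 6: p = 0.028

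So 4 of 66 app users (6%) are enough by uncorrected chi-squared, and 6 of 66 (9%) by Fisher. Neither count depends on what controls do at home.

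The chance of a significant result is P(X ≥ 4) or P(X ≥ 6) with X binomial (66, p). The article does not give p, the share of app users reaching 25, so a range is shown:

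| p (assumed) | Uncorrected chi-squared | Fisher |
|---|---|---|
| 5% | 42.1% | 11.2% |
| 10% | 90.7% | 65.7% |
| 20% | 99.97% | 99.5% |
| 30% | >99.99% | >99.99% |

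**4. If control scores are treated as missing**

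No control value is observed at any visit. Multiple imputation then has nothing in that arm to learn from, and any imputed control score is purely a product of the model's assumption.

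**5. Baseline adjustment**

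No app score exists before visit 2 in either arm. If baseline is coded zero for everyone, the covariate is constant and adjusts nothing. If it is left missing, the planned covariance analysis cannot be fitted.

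**The case against.** The strongest reply is that the article may not intend the app to be the sole measure. The abstract and Study setting tie this outcome to the questionnaire assessments, Primary outcomes/behavioral lists monitoring among the assessed behaviours, and Outcome measures omits the app. The questionnaire items are not shown, and an article condenses a fuller protocol, so an item asked in both arms may exist. This stands: a reader might infer that monitoring is measured by the app and nothing else, and the documents do not establish that. What remains is a contradiction, because the only score, threshold and schedule row given all point to the app.

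A second reply is that the section on monitoring states no between-arm test, and Intervention delivery treats server data as a stand-in for how well the intervention is followed. The app score could therefore be an intervention-arm process measure. That is plausible, but the score is placed under primary outcomes, and Statistical methods applies its comparisons without exception.

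A third reply concerns size. A reader might infer a certain false positive, or a rate of essentially 100%. Neither is supported. A false positive needs controls to be scored zero and enough app users to reach 25. At 10% reaching it, Fisher is significant in about 66% of trials, and if control scores are missing there is no test at all.

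Finally, Sample size rests on the Hill-Bone scale, so the powered comparison does not depend on this score. That also stands, and it limits the reach of the point.

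**Conclusion.** The point holds as a contradiction with a concrete consequence. The one scoring rule given cannot yield a value for controls or a baseline value for anyone, while other sections call for a questionnaire-type outcome at three time points and a baseline-adjusted comparison.

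Applied as written, the rule leads to one of two results. With controls scored zero, significance arises in about 66% to over 99.9% of trials by Fisher, or 91% to over 99.9% by uncorrected chi-squared, even if home monitoring is identical in both arms. With controls missing, no comparison is possible. The percentages assume 66 analysed per arm and 10% to 30% of app users reaching 25.

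The defect is confined to this headline outcome and leaves the Hill-Bone comparison untouched. It should be settled before any between-arm result on monitoring is reported.

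**What to change.** Reconcile Regular BP monitoring and Table 1 with the abstract, Study setting, Primary outcomes/behavioral, Outcome measures and Statistical methods, as follows.

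- Define the between-arm outcome as frequency of home BP monitoring, taken from the same questionnaire item(s) in both arms at baseline, week 8 and week 24, and analyse it with baseline adjustment.
- If the questionnaire already holds such an item, name it. If not, add one or two.
- Report the 60-day app score (maximum 30 if one point per entry) descriptively, in the intervention arm only, as a measure of engagement. State the points per entry, and remove the visit 1 mark from that row of Table 1.

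The questionnaire visits already exist in both arms, so the direct cost is small. There are two real downsides. The outcome becomes self-reported, a limitation that the Discussion already accepts for the questionnaire. And because Trial status says recruitment is under way, participants already enrolled may lack a baseline value if the item does not yet exist. The plan should say in advance how those participants enter the adjusted analysis.

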#### Smoking cessation

This will be evaluated through a couple of questions in the questionnaire, at the baseline assessment and at the 8^th^ and 24^th^ weeks.

#### Predisposing factors, enabling factors and reinforcing factors of adherence

Some of the questions of the questionnaire assess these factors. These measurements are performed at the baseline assessment and at the 8^th^ and 24^th^ weeks. A 20 % increase in score is considered desirable.

## Outcome measures

The primary outcomes of the intervention will be measured by, the researcher-made questionnaire, a manual sphygmomanometer, a weighing scale, a measuring tape, and biological tests.

### Questionnaire

The questionnaire contains the patient’s personal and demographic information, treatment status, and certain health-related behaviors as the baseline assessment. In creating it, we have used some of the constructs taken from the Predisposing, Reinforcing and Enabling Constructs in Educational Diagnosis and Evaluation (PRECEDE) model (predisposing, enabling and reinforcing factors), the WHO STEPS questionnaire for monitoring of chronic diseases risk factors [12], the Hill-Bone High Blood Pressure Therapy Compliance Scale [9], and the International Physical Activity Questionnaire (IPAQ) [13].

## Participants

The participants are hypertensive patients who have been diagnosed by a physician. The inclusion criteria are, age 30 to 60 years, treatment for HTN in the past year, having a smart phone and the ability to use it, sufficient literacy, inclination to participate in the study, and residence at the study’s location in the first 6 months of the study. The exclusion criteria include having had complications of HTN, such as myocardial infarction, cardiac insufficiency and other cardiovascular diseases, diabetes, and other physical disabilities. After obtaining informed consent from all the participants, their inclusion criteria will be evaluated by a physician. Then, the baseline data will be collected by the abovementioned (baseline data) questionnaire.

### Sample size

The sample size is 120 (60 persons in each group) with a power of 80 % to detect a minimum difference of five scores (a mean of 40 and 45 in the control and intervention groups and a standard deviation of 10). Based on the Hill-Bone High Blood Pressure Therapy Compliance Scale [9], the mean difference was calculated with the two-tailed test at a significance level of 5 %. Bearing in mind the possibility of sample loss, 10 % was added to the sample size and 132 persons were estimated.

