### Randomization

The participants will be randomly assigned to two groups after the initial examination and upon completing the baseline data form. Random sequencing will be done in blocks of 4 using the randomization website at http://www.jerrydallal.com/random/permute.htm. The ratio of assignment to each arm will be 1:1 and each group will have 66 individuals.

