## Statistical methods

The qualitative findings of the study will be described using frequency and percentage frequency, and the quantitative findings will be described using mean and standard deviation. To analyze the effectiveness of the main outcome variable of the study, we will use analysis of covariance (comparison of mean changes in score of the adjusted questionnaire – based on the baseline score at the beginning of the study and other possible confounding factors) at a confidence interval of 95 %. This approach will be repeated for all the quantitative variables.

The remaining qualitative variables of the study will be compared by the chi-squared test between the two groups. The main approach of the study will be intention-to-treat. The final results will be analyzed per protocol. Lost data will be replaced through multiple imputation techniques.

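### 60 per arm gives about 77.5% power, not the stated 80%, for 5 points with SD 10, and adding 10% for loss leaves just under 60 per arm

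*Protocol article*

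**What the plan says.** The Sample size section gives every input to the calculation:

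- Size and power: "The sample size is 120 (60 persons in each group) with a power of" 80%.
- Effect: "to detect a minimum difference of five scores (a mean of 40 and 45 in the control and intervention groups", measured on the Hill-Bone compliance score, with the SD taken as 10.
- Test: "the mean difference was calculated with the two-tailed test at a significance level of" 5%.
- Loss: 10% "was added to the sample size and 132 persons were estimated".

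The Randomization section carries the total forward: "The ratio of assignment to each arm will be 1:1 and each group will have 66 individuals".

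For the main outcome variable, the Statistical methods section says "we will use analysis of covariance", adjusting for the baseline score. The sample-size paragraph mentions neither this adjustment nor a correlation between baseline and follow-up scores.

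**The concern.** This is a comparison of two means with all inputs stated, so the number per arm can be recomputed, and 60 looks too small for a standardised difference of 5/10 = 0.5. Adding 10% to the required number also does not protect that number against a 10% loss.

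The 80% figure is the only justification given for the size of the trial. If it is wrong, a null result will be read against power that the design does not have under its own assumptions.

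**Working it through.** **Inputs** (Sample size section): difference δ = 45 − 40 = 5; SD σ = 10; two-sided α = 0.05 (z = 1.960); power 80% (z = 0.842); 60 per arm; 10% added for loss. From the Randomization section: 66 per arm, 1:1.

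**1. Can 60 per arm be reproduced?**

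n per arm = 2(1.960 + 0.842)²σ²/δ² = 2 × 7.849 × 100/25 = 62.8, so 63 per arm (126 in total).

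The exact calculation with the noncentral t distribution gives 63.8, so 64 per arm (128 in total).

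Variants tried:
- Rounded values 1.96 + 0.84: 62.7, again 63.
- One-sided 5%: 50 per arm, which also contradicts the stated two-tailed test.

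None of these gives 60.

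**2. Power at the numbers in question** (δ = 5, σ = 10, two-sided 5%, unadjusted comparison)

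| Per arm | t test | Normal approximation |
|---|---|---|
| 59.4 | 77.1% | 77.8% |
| 60 | 77.5% | 78.2% |
| 63 | 79.5% | 80.1% |
| 64 | 80.1% | 80.7% |
| 66 | 81.4% | 81.9% |

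The difference detectable with 80% power by t test is 5.16 points at 60 per arm and 5.18 at 59.4 per arm.

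**3. The loss step**

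- The plan's figure reproduces as 120 × 1.10 = 132.
- A 10% loss from 132 leaves 132 × 0.90 = 118.8, or 66 × 0.90 = 59.4 per arm.
- 132 preserves 120 only if the loss is at most 12/132 = 9.1%.
- To keep 120 after 10% loss: 120/0.90 = 133.3, so 134.
- With the corrected requirement: 126/0.90 = 140 (70 per arm), or 128/0.90 = 142.2, so 143, which becomes 144 with equal arms (72 per arm).

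**4. The planned covariance analysis**

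Adjusting for a baseline score with correlation r to follow-up multiplies the residual variance by about (1 − r²), so the required number falls to about 63.77(1 − r²) per arm on the t-test scale. Setting this equal to the number available:

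- 60 per arm: r = √(1 − 60/63.77) = 0.24.
- 59 per arm: r = √(1 − 59/63.77) = 0.27.

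At 59 per arm, r = 0.5 gives about 87.5%. The protocol states no r, so these values are assumptions that show the range.

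**The case against.** The strongest reply is that 77.5% describes an unadjusted t test, which is not the planned main analysis. The protocol plans analysis of covariance on the baseline score, so leaving the covariate out makes the calculation conservative, and a modest correlation of about 0.24 to 0.27 restores 80%. This stands to the extent that the trial has not been shown to be underpowered for its planned analysis. It does not rescue the statement: the paragraph uses no covariate and gives no correlation, so 80% does not follow from what is written.

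The gap is also small: 1.8 points by the normal approximation, 2.5 by the t test, and less than 0.2 points on a score running from 14 to 56. The SD of 10 is a round planning value, and uncertainty in it could outweigh this gap. That is fair, and it limits the weight of the finding. Both methods still fall below 80%.

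The loss step is the lesser part. The text can be read as simply adding 10% without claiming that 10% of those randomised will be lost. Even on the stricter reading the deficit is two patients (132 against 134) and 0.4 points of power.

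Finally, 66 per arm gives 81.4 to 81.9%, but only with no loss. Using it to defend 80% would spend the loss allowance twice.

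**Conclusion.** The concern holds. Under the protocol's own inputs, 80% power needs 63 to 64 per arm. The stated 60 gives 77.5% (t) or 78.2% (normal), and about 77 to 78% remains if 10% of the 132 are lost. Correctly done, the same two-sample calculation with 10% loss would randomise 140 to 144, which is 8 to 12 more than planned.

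This is an arithmetic error in the stated justification, of modest size. It rests on δ = 5, SD 10, a two-sided 5% test and no covariate adjustment, all as the paragraph gives them. The figures after loss also assume that the 10% is the expected proportion lost. Power under the planned covariance analysis cannot be fixed from the document, because it depends on a correlation that is not given.

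**What to change.** Keep 132 patients and correct the paragraph in one of two ways.

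1. **Restate the power for the unadjusted comparison.** Suggested wording: with 118 to 120 participants analysed, a two-sided 5% t test has about 77% power for a difference of 5 points (SD 10), and 80% power for about 5.2 points.
2. **Base the calculation on the planned analysis of covariance.** State the assumed correlation between baseline and follow-up scores, with its source, and show power over a range. About r = 0.27 is needed for 80% at 59 per arm, and r = 0.5 gives about 87%. The value should come from evidence and should not be chosen because it returns 80%.

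In either case, write the loss step as n/(1 − 0.10) and say that the 10% is the expected proportion lost. The figure of 118 to 120 analysed is only as secure as that 10%, so it should be considered alongside the list in the Withdrawal criteria section.

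The cost is rewording one paragraph. The stated power becomes slightly less favourable, or it rests on an explicit assumption. Recruitment, allocation and analysis do not change.
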